### Missing Data and Dropouts

Although treating individuals lost to follow-up as presumed smoking is a widely used strategy in smoking cessation studies (ie, intention-to-treat), there are potential problems with this approach, especially when comparing interventions with differential dropout rates [132]. Therefore, we will conduct sensitivity analyses to test for treatment efficacy, assuming different missing data mechanisms. For example, we will consider a multiple imputation approach based on smoking-related participant characteristics at baseline, as well as demographics, to account for potential missing-at-random mechanisms. We will also explore pattern-mixture and selection models to account for potential missing-not-at-random mechanisms [133].

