## Methods

### Design Overview

This study will use a 2-group RCT to compare ST with AT. We will enroll a total of 500 participants (250/500, 50% per group). An additional 20 participants (10 per group) will be enrolled in a 12-week pilot study before the implementation of the full trial. All participants will be recruited on the web from Florida. Participants will complete assessments on the web via the Research Electronic Data Capture (REDCap) platform (Vanderbilt University) hosted at H. Lee Moffitt Cancer Center and Research Institute [42,43] or over the phone at baseline and at 3, 6, and 12 months postenrollment. These assessments will take approximately 20 minutes to complete. Weekly 4-item smartphone assessments will be collected from all participants for 26 weeks.

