### Primary Aim

The primary aim of this study is to evaluate the efficacy of AT in facilitating smoking cessation among people with HIV. We hypothesize that at 12 months postenrollment, smoking abstinence rates will be higher in the AT group than in the ST group. The primary outcome is self-reported 7-day point prevalence abstinence at 12 months. As is traditional in smoking cessation research, participants who do not complete a follow-up will be coded as smoking. Log-binomial regression will be used, with the intervention group (AT vs ST) as the primary predictor. Variables found to differ by group in preliminary analyses (*P*<.10) will be included as covariates. Differences in treatment effects as a function of sex assigned at birth will also be examined.

Additional analyses will evaluate the effects of the intervention on other definitions of smoking abstinence: biochemically verified abstinence using salivary cotinine and self-reported 24-hour, 30-day, and continuous abstinence. Outcomes from the 3- and 6-month follow-ups will also be considered. Repeated-measures analysis using generalized linear mixed models with a log-link function and the appropriate random-effect covariance structure will be used to analyze outcomes across all assessments with intervention, time, and their interaction as the primary model variables. Model fitting and diagnostics will follow the general approach described by McCullagh and Nelder [113] and McCulloch et al [114], when applicable. Adjustments for multiple comparisons will be made using the methods recommended by Westfall and Young [115].

### Secondary Aim 1

The first secondary aim is to explore the role of potential mediators and moderators. Specifically, we will compare the magnitude of the mediated effects via common mechanisms (ie, motivation, agency, and stress or negative affect) on smoking abstinence between the AT and ST groups. We will also investigate the role of several established HIV-specific moderators (ie, stigma, resilience, disease progression, and HIV symptom burden). Furthermore, exploratory analyses will examine the associations of various AT treatment components with outcomes.

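### The one missing-at-random imputation described names only baseline predictors and not the interim smoking status the trial collects; if dropout follows relapse and differs by arm, it can bias the contrast it is meant to check

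*Protocol article*

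**What the plan says.** Under Primary Aim, the protocol article defines the endpoint: "The primary outcome is self-reported 7-day point prevalence abstinence at 12 months". The rule for missing data is that "participants who do not complete a follow-up will be coded as smoking".

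Missing Data and Dropouts acknowledges the weakness of that rule: "there are potential problems with this approach, especially when comparing interventions with differential dropout rates". It therefore promises sensitivity analyses under different missingness mechanisms. As an example, "we will consider a multiple imputation approach based on smoking-related participant characteristics at baseline, as well as demographics", the purpose being "to account for potential missing-at-random mechanisms". It adds: "We will also explore pattern-mixture and selection models to account for potential missing-not-at-random mechanisms".

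On the data available, Design Overview states: "Weekly 4-item smartphone assessments will be collected from all participants for 26 weeks". The ST Group and AT Group sections list smoking status among the weekly items in both arms. Table 1 also schedules smoking status at 3, 6 and 12 months, and Primary Aim says "Outcomes from the 3- and 6-month follow-ups will also be considered".

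**The concern.** Missing at random is an assumption conditional on whatever enters the imputation model. It is most credible when that model contains the variables that predict both dropout and the 12-month outcome. In a cessation trial, the obvious candidate is whether the participant had quit or relapsed when last seen. Everyone enrolled smokes at least five cigarettes a day, so smoking status does not vary at baseline, and baseline variables can say only indirectly who later relapsed. The Introduction reports high long-term relapse in the team's earlier studies, with effects diminished by 6 months, so dropout after relapse is a realistic possibility.

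If relapsed participants leave more often, an imputation that does not see the relapse gives them roughly the abstinence rate of those who stayed. Abstinence is then overstated in each arm. If this selective dropout is heavier in one arm, the overstatement is unequal and the contrast moves. Differential dropout is the article's own reason for running sensitivity analyses, so a faulty check there could wrongly contradict or wrongly support the primary result.

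**Working it through.** **The plan's own figure.** Power Considerations states 80% power for 5% vs 12% with 250 per group, two-sided 0.05. With pooled variance under the null, z = [0.07·√250 − 1.96·√(2·0.085·0.915)] / √(0.05·0.95 + 0.12·0.88) = (1.1068 − 0.7730)/0.3913 = 0.853, so power is 80.3%. The figure reproduces and does not involve the imputation model.

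**Model for the check.** In each arm let q be the proportion abstinent at an interim visit, a and b the 12-month abstinence probabilities of interim abstainers and interim smokers, and d1 and d0 their dropout probabilities. Dropout depends on interim status only.

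- Truth: p = q·a + (1−q)·b
- Missing = smoking: N = q(1−d1)a + (1−q)(1−d0)b
- Within-arm imputation with uninformative baseline variables (the completers' rate): N / [q(1−d1) + (1−q)(1−d0)]
- Imputation conditioning on interim status: q·a + (1−q)·b, the truth, because a and b are estimated without bias from completers

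The article gives none of q, a, b, d1 or d0. All are assumptions.

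**Example 1, no true effect.** q = 0.22, a = 0.70, b = 0.05, d1 = 0.10 in both arms; d0 = 0.35 in ST and 0.20 in AT.

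- Truth: 0.22·0.70 + 0.78·0.05 = 0.154 + 0.039 = 19.3% in both arms.
- ST: N = 0.22·0.90·0.70 + 0.78·0.65·0.05 = 0.16395; retained 0.198 + 0.507 = 0.705; imputed 0.16395/0.705 = 23.3%.
- AT: N = 0.1386 + 0.78·0.80·0.05 = 0.1698; retained 0.198 + 0.624 = 0.822; imputed 0.1698/0.822 = 20.7%.
- AT minus ST: −2.6 points, risk ratio 0.89. Missing = smoking gives 16.4% vs 17.0%, +0.6 points.
- With d0 = 0.40 in ST: 0.162/0.666 = 24.3%, so −3.7 points, risk ratio 0.85.

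**Example 2, planning rates and a second null.** a = 0.60, b = 0.02, d1 = 0.10; q = (p − b)/(a − b). Differences are AT minus ST, in points.

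| True ST, AT | d0 ST, AT | Baseline-only imputation | Difference, RR | Missing = smoking: difference, RR |
|---|---|---|---|---|
| 5%, 12% | 0.30, 0.30 | 5.8%, 14.3% | 8.5, 2.46 | 6.3, 2.54 |
| 5%, 12% | 0.20, 0.40 | 5.4%, 15.8% | 10.5, 2.95 | 6.0, 2.39 |
| 5%, 12% | 0.40, 0.20 | 6.4%, 13.0% | 6.6, 2.04 | 6.7, 2.71 |
| 10%, 10% | 0.20, 0.40 | 10.8%, 13.2% | +2.4, 1.22 | −0.3, 0.96 |
| 10%, 10% | 0.30, 0.30 | 11.9%, 11.9% | 0.0, 1.00 | 0.0, 1.00 |

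The true contrast in the first three rows is 7.0 points, RR 2.40.

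**Range.** The planning-rate cases were repeated with (a, b) = (0.70, 0.02) and (0.50, 0.03). With the same interim-dependent dropout in both arms, the imputed RR lies between 2.46 and 2.58 and the difference between 8.4 and 9.6 points. With dropout patterns that differ by arm, the RR lies between 2.04 and 3.19. With 20% dropout regardless of interim status, baseline-only imputation returns 5.0% vs 12.0%, with no bias.

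**Simulation.** Rows 1, 2 and 4 of the table were simulated (250 per arm, 600 trials, 20 imputations). Baseline-only imputation gave 8.4, 10.5 and 2.3 points; adding interim status gave 6.9, 7.0 and 0.0.

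**The case against.** The strongest reply is that the sentence is an illustration in a condensed article. It is introduced as an example of what will be considered, and a full predictor list normally belongs in an analysis plan that is not shown. This stands in part. A reader might infer that interim smoking status is excluded; the text excludes nothing. But it does go as far as naming a predictor set, that set is placed at baseline, and it is the only missing-at-random analysis described.

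A reader might also infer that treatment arm is left out of the imputation, since the sentence does not list it. The documents do not support that: the sentence describes participant characteristics, and silence about the variable under test is not omission.

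Third, other analyses are planned. The pattern-mixture and selection models mean this imputation is not the sole check on the missing-equals-smoking rule, but they address a different mechanism and do not repair a weak missing-at-random analysis. The mixed model under Primary Aim uses outcomes across assessments and, if fitted to observed data only, would draw on interim status. It is not offered as a missing-data analysis, and the article does not say whether missing visits are coded as smoking there.

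Fourth, the examples are favourable to the concern. They treat baseline variables as uninformative, whereas the article itself calls self-efficacy a strong predictor of treatment outcome and measures it at baseline. They also assume interim status is known for every dropout. Both points stand: predictive baseline variables would shrink the bias, though not generally remove it, and relapse after the last report stays missing not at random whatever enters the imputation.

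**Conclusion.** The point holds in a limited form. The missing-at-random analysis as described does not name the most relevant data the trial collects. When dropout depends on interim smoking and differs by arm, it can mislead in either direction and can land further from the truth than the rule it checks: in the null examples, −2.6 points against +0.6, and +2.4 against −0.3.

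These sizes rest on assumed dropout and transition rates, uninformative baseline variables and fully known interim status; they are not predictions for this trial. With similar dropout patterns in both arms, abstinence is still overstated but the risk ratio barely moves. If dropout is unrelated to interim status there is no bias.

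A reader might go further and conclude that the sensitivity analysis is certain to be biased or that the trial's main result is compromised. Neither follows. The bias is conditional, one of several sensitivity analyses is affected, and the primary analysis, its missing-data rule and the stated power are untouched.

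**What to change.** State that the imputation model will include treatment arm, the stratification factors, baseline smoking variables and demographics, plus 3- and 6-month abstinence and a summary of the weekly smoking reports, for example the last reported status. Imputing within arm, or with arm interactions, would let the relation between interim and final status differ by arm. Interim reports that are themselves missing would be imputed in the same procedure.

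Keep the pattern-mixture and selection models for relapse after the last report, which no missing-at-random model can recover.

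The cost is a sentence or two of analysis-plan wording and a little more programming. All the data are already scheduled for collection in both arms, and the sample size does not change.

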### Power Considerations

Because an intention-to-treat approach will be used for our primary analysis, and participants lost to follow-up will be classified as smokers, our power calculation assumes a sample size of 500 (250/500, 50% per group). Power is based on the primary aim of comparing self-reported abstinence rates between AT and ST at the 12-month follow-up [134]. On the basis of findings from our AAC implementation study [24,25], we expect 5% abstinence in ST. Assuming a sample size of 250 per group, a 2-group large-sample normal approximation test of proportions with a 2-sided 0.05 significance level will have 80% power to detect an increase in abstinence of 7% in AT compared with ST. Simulation studies using similar and smaller samples have demonstrated that bootstrap resampling approaches are more powerful than other approaches for estimating indirect effects and conditional indirect effects [135-137]. Therefore, we expect to have sufficient power to detect effects.

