### Quitline-Delivered Smoking Cessation Treatment in Vulnerable Populations

Our team developed an approach to link smokers in health care settings with evidence-based treatment delivered via state quitlines. This approach—Ask Advise Connect (AAC)—links smokers with treatment via an automated connection system. Results from efficacy trials revealed that AAC was associated with a 13- [22] to 30-fold [23] increase in treatment enrollment when compared with Ask Advise Refer, where smokers were offered a quitline referral and encouraged to call on their own. We have successfully implemented AAC in various settings (eg, safety-net hospitals and HIV clinics) throughout Texas and Oklahoma [24,25].

While the results are encouraging, several factors suggest that interventions such as AAC that depend on connecting smokers with quitlines may not be sufficient. First, in recent years, state quitlines have experienced significant budget cuts, and some states have temporarily eliminated quitlines altogether [26-28]. Moreover, while quitlines provide a cost-effective and evidence-based treatment option and have the potential to reach countless smokers [29], human-delivered phone counseling has limited appeal. In fact, national data suggest that quitlines reach only 1% to 2% of smokers [30]. Finally, results from a recent AAC implementation study indicated that self-reported abstinence was 18.7% among HIV clinic patients and 16.5% among non–HIV clinic patients; however, biochemically confirmed abstinence was considerably lower (4.2% and 4.5%, respectively) [24,25]. There is a critical need to improve the reach, efficacy, sustainability, and impact of smoking cessation treatment for people with HIV [31].

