#### Primary Outcomes

The main outcome is self-reported 7-day abstinence smoking status at the 12-month follow-up. Other definitions of abstinence, such as biochemically verified abstinence using salivary cotinine and self-reported 24-hour, 30-day, and continuous abstinence, will be examined as secondary outcomes. Participants who report 7-day abstinence will be mailed a cotinine kit with instructions for providing the cotinine sample. Study staff will be available by phone and email if participants have questions about the collection process. Participants will be asked to return cotinine samples using a prepaid envelope.

All participants (ST and AT) will complete brief smartphone-delivered assessments each week during the 26-week treatment period. These assessments will be delivered to AT participants through the app, while ST participants will receive their assessments through a REDCap link. Regardless of the treatment group, assessments will be identical and include current smoking status, motivation, agency, and stress or negative affect. Responses to the assessments will be used to select the appropriate treatment content for AT participants, as described above.

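### The power calculation for the self-reported primary outcome uses a 5% control rate that the cited study, as the protocol reports it, does not support for self-report

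*Protocol article*

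**What the plan says.** The Primary Aim section fixes the endpoint: "The primary outcome is self-reported 7-day point prevalence abstinence at 12 months". Participants without a follow-up are coded as smoking. Under Primary Outcomes, cotinine-verified abstinence is placed among the secondary measures: "Other definitions of abstinence, such as biochemically verified abstinence using salivary cotinine and self-reported 24-hour, 30-day, and continuous abstinence, will be examined as secondary outcomes".

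Power Considerations refers to the same endpoint: "Power is based on the primary aim of comparing self-reported abstinence rates between AT and ST at the 12-month follow-up". It then sets the control rate: "On the basis of findings from our AAC implementation study [24,25], we expect 5% abstinence in ST". With 250 per group, a two-sided 0.05 level and a normal-approximation test of two proportions, it claims 80% power for an increase of 7% in AT.

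The Introduction, in the section on quitline-delivered treatment, describes the same implementation study under the same two references: "self-reported abstinence was 18.7% among HIV clinic patients and 16.5% among non–HIV clinic patients". The sentence goes on to say that "biochemically confirmed abstinence was considerably lower (4.2% and 4.5%, respectively" for the two clinic groups.

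**The concern.** The control rate is presented as an expectation for self-reported abstinence and is credited to one study. As the protocol itself reports that study, self-reported abstinence was more than three times as high (16.5% and 18.7% against 5%). The figures close to 5% are the biochemically confirmed ones, so the input appears to have been taken from a different outcome than the one being tested.

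This matters because the variance of a proportion grows as the rate rises from 5% towards 20%. A fixed absolute difference is then harder to detect with the same number of participants. The paragraph is the only justification given for 500 participants. If the control rate turns out well above 5%, a non-significant result could be read as evidence against a 7-point benefit from a trial with 80% power, when its power for that benefit was lower.

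**Working it through.** **Inputs.** From Power Considerations: n = 250 per group, two-sided alpha 0.05 (z = 1.960), ST rate 5%, increase 7%. From the Introduction: self-reported rates 18.7% and 16.5%. Assumed here: an ST rate of 10%, as an intermediate value, because the Introduction does not say when or with what missing-data rule the 18.7% was measured.

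The 7% is read as percentage points. As a relative increase (5% to 5.35%), power would be under 4%.

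**Formula.** With p1 for ST, p2 for AT and m = (p1 + p2)/2:

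power = Φ{ [ (p2 − p1)√n − 1.960 √(2m(1 − m)) ] / √(p1(1 − p1) + p2(1 − p2)) }

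For a 7-point difference, (p2 − p1)√n = 0.07 × √250 = 1.1068 throughout.

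**Step 1: reproduce the stated figure.** p1 = 0.05, p2 = 0.12, m = 0.085.
- 1.960 × √(2 × 0.085 × 0.915) = 0.7730
- √(0.0475 + 0.1056) = 0.3913
- (1.1068 − 0.7730)/0.3913 = 0.853, so power = 80.3%

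The stated 80% is confirmed. Unpooled variance gives 80.7% and exact enumeration of the pooled test 81.5%.

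**Step 2: use the self-reported rate for HIV clinic patients.** p1 = 0.187, p2 = 0.257, m = 0.222.
- 1.960 × √(2 × 0.222 × 0.778) = 1.1519
- √(0.1520 + 0.1910) = 0.5856
- (1.1068 − 1.1519)/0.5856 = −0.077, so power = 46.9%

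Exact enumeration gives 47.1%.

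**Step 3: the range.** The detectable difference is the value of p2 − p1 at which the formula returns 0.80 with n = 250. The risk ratio is (p1 + difference)/p1.

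| ST rate | Power for +7 points | Difference detectable at 80% | Risk ratio |
|---|---|---|---|
| 5% (Power Considerations) | 80.3% | 7.0 points | 2.39 |
| 10% (assumed) | 63.0% | 8.8 points | 1.88 |
| 16.5% (non-HIV clinics) | 49.9% | 10.3 points | 1.62 |
| 18.7% (HIV clinics) | 46.9% | 10.7 points | 1.57 |

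Closer to 5%, power for +7 points is already 76% at an ST rate of 6% and 71% at 7.5%.

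**Step 4: the ratio scale.** The planned contrast is a risk ratio of 12/5 = 2.4. Held constant, it gives 10% versus 24% (98.8% power) and 18.7% versus 44.9% (over 99%). Power therefore falls for a fixed absolute difference and rises for a fixed ratio.

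**The case against.** Four points can be made in defence of the plan.

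First, the protocol never calls the 5% a verified rate. It says only that the figure rests on findings of the study, and 5% equals none of the four reported rates. This stands: a reader might infer as fact that the verified rate was substituted, but that is an inference from proximity. The mismatch with the reported self-reported rates does not depend on it.

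Second, 18.7% need not be the 12-month ST rate in this trial. The Introduction gives no follow-up time, denominator or missing-data rule for it. The trial counts non-completers as smoking, and the team reports high long-term relapse in its earlier work. This also stands, so the documents do not support a flat statement that the trial has 47% power. It does not rescue 5% unexplained. If 18.7% is a rate among responders, missing-as-smoking alone would have to remove 1 − 5/18.7, about 73% of participants, to reach 5%. The protocol assumes no such loss.

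Third, the primary model is log-binomial and so estimates a risk ratio. At 18.7% the trial can detect 1.57, a smaller ratio than the 2.4 planned. This is correct and belongs in the restated paragraph. However, the plan states its effect only as an increase of 7%, and a ratio of 2.4 on 18.7% would need about 45% abstinence in AT.

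Fourth, a reader might conclude that verified abstinence should become the primary outcome so that it fits the 5%. The documents give no ground for this. It would change what is estimated, make the result depend on mailed kits sent only to those reporting abstinence, and depart from the self-report used in the economic evaluation.

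**Conclusion.** The concern holds as an inconsistency between the control rate and the endpoint, not as an arithmetic error. The 5% is credited to a study whose self-reported rates, as the protocol gives them, are 16.5% and 18.7%, and no justification links those rates to 5%.

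For the stated 7-point increase with 250 per group, power is below 80% at any ST rate clearly above 5% in the range considered. It reaches 46.9% if the HIV-clinic self-reported rate applies unchanged. The size of the shortfall rests on two assumptions: the true 12-month, missing-as-smoking ST rate, which the documents do not settle, and an effect held constant in percentage points, as the plan words it.

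**What to change.** Restate Power Considerations for self-reported abstinence over an ST range of about 5% to 18.7%. Suggested wording: With 250 per group and a two-sided 0.05 level, the trial has 80% power to detect an increase of 7.0 percentage points (risk ratio 2.39) if 12-month self-reported abstinence in ST is 5%, 8.8 points (1.88) if it is 10%, and 10.7 points (1.57) if it is 18.7%.

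Alternatively, keep 5% and explain why it is a reasonable 12-month self-reported rate with missing counted as smoking, stating the timing and missing-data handling of the 18.7%. In either case, write the effect in percentage points, and say that power for a fixed 7-point increase falls as the ST rate rises, whereas power for a fixed ratio of 2.4 does not.

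The cost is one rewritten paragraph and a less favourable stated detectable difference. Sample size, primary outcome and analysis stay as they are.
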